## Abstract

**Background/Objectives**: Physical exercise (PE) has been shown to have positive effects on the symptoms associated with autism spectrum disorder (ASD). However, there is still no consensus on the most appropriate PE intervention model. With this in mind, we developed a program with the aim of determining the effects of PE on physical fitness, with a view to applying it as a potential treatment. **Methods**: Using an experimental methodology, this research work will recruit 18 institutionalized young people and adults who will be allocated to one of two groups, namely (i) the youth training group and (ii) the adult training group, using low-cost materials. Both intervention groups will perform 90 min of training per session, twice a week, for 12 weeks. Evaluations will be carried out at baseline and month 3. The impact of the exercise program will be assessed based on the variables of anthropometry, body composition, cardiovascular response, and cardiorespiratory fitness. **Results**: The results of this study will contribute to the development of more effective strategies, prescription recommendations, and interventions as a guarantee in future programs of better and greater adherence to PE by institutionalized individuals with ASD. **Conclusions**: In addition, we intend to make the PE program available if it promotes positive effects in the target population.

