### 2.5. Intervention Assignment and Blindness

Once the initial assessments have been completed, the volunteers will be allocated to the two groups according to their age group. Due to the nature of the intervention, it will not be possible to randomize the sample into groups nor to “blind” participants and the principal investigator.

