#### 3.1.11. Statistical Analysis

Descriptive parameters such as the mean and standard deviation will be used in the statistical analysis. The normality of the data will be checked using the Shapiro–Wilk test. Significant differences between groups will be analyzed using the Kruskal–Wallis test, while differences between assessment times will be investigated using the Wilcoxon test. The choice of non-parametric statistics is based on the central limit theorem, which suggests that in order to obtain a normal distribution, a minimum sample size of 30 participants is required [53]. The magnitudes of the differences will be assessed by Cohen’s d effect size [54]. In addition, associations between study variables will be checked using Spearman’s correlation coefficient [55]. The significance level adopted for all analyses will be *p* < 0.05. The data will be processed using the Statistical Package for the Social Sciences (SPSS) software, version 28, Chicago, IL, USA.

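### Uncorrected Cohen's d does not match the planned rank tests and is biased upwards at this sample size; the stated reason for those tests and the normality check beside them also need rewording

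*Protocol article*

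**What the plan says.** The protocol article's section 3.1.11 (Statistical Analysis) contains all of the wording at issue.

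- **Normality:** "The normality of the data will be checked using the Shapiro–Wilk test". No rule says what follows from the result.
- **Tests:** "Significant differences between groups will be analyzed using the Kruskal–Wallis test, while differences between assessment times will be investigated using the Wilcoxon test". Associations use Spearman's coefficient. No parametric alternative is named.
- **Reason:** "The choice of non-parametric statistics is based on the central limit theorem, which suggests that in order to obtain a normal distribution". The condition in full is that "in order to obtain a normal distribution, a minimum sample size of 30 participants is required".
- **Effect measure:** "The magnitudes of the differences will be assessed by" Cohen's d. The text names no small-sample correction and no standardising SD.

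On size, the Abstract says "this research work will recruit 18 institutionalized young people and adults who will be allocated to one of two groups". Section 2.5 adds that "the volunteers will be allocated to the two groups according to their age group". The number expected in each group appears nowhere. Section 2.1 sets two assessments, at weeks 0 and 12, so the within-group comparison is paired.

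**The concern.** Three parts of one short section do not fit together.

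1. The central limit theorem describes the sampling distribution of a mean. It says nothing about raw data becoming normal, sets no threshold at 30, and does not oblige anyone to use rank tests below that number.
2. With 18 recruits, the section's own rule of 30 has settled the choice of tests before any data are seen. The Shapiro–Wilk result therefore has nothing to decide.
3. Having chosen rank tests, the section measures magnitude with a statistic built on means and SDs. The p-value and the effect size then answer different questions and can point different ways. At this size uncorrected d also overstates the true standardised effect on average.

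What is at stake is the reported magnitude. The Discussion calls the work a pilot, there is no control group, and the article states no power calculation. Readers will therefore look closely at the effect sizes, which should match the tests beside them and have one clear definition.

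**Working it through.** **Inputs.** Total of 18 (Abstract); allocation by age with no group sizes (section 2.5); two time points (section 2.1); tests, effect measure and the 0.05 level (section 3.1.11). A 9/9 split is assumed as 18/2. The figure of 30 has no formula or inputs behind it, so there is nothing to reproduce.

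**Step 1: the rule of 30.** Two simulations test it from each side.
- Lognormal data with sigma 1, n = 30: the raw data stay heavily skewed, and even the mean has skewness of about 1.08. With sigma 0.5 the mean's skewness is about 0.31. Thirty is not a guarantee.
- Normal data, n = 9: the t-test rejects a true null in 4.9% of samples, against a nominal 5%. Fewer than 30 does not by itself require ranks.

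**Step 2: the normality check.** Every test named is rank-based, so neither outcome of Shapiro–Wilk changes the analysis. It would also be weak here. At n = 9 it rejects about 40% of exponential samples and 22% of lognormal (sigma 0.5) samples; at n = 18, about 78% and 47%.

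**Step 3: mismatch between d and the rank test.** Take nine invented changes: 0.9, 1, 1.01, 1.02, 1.03, 1.1, 1.2, 1.3 and 20. All are positive, so the exact two-sided Wilcoxon p is the smallest possible, 2/2⁹ = 0.0039. The mean is 28.56/9 = 3.17 and the SD is 6.31, so d = 3.17/6.31 = 0.50. The median change is 1.03. One extreme value raises both mean and SD, so d looks moderate while the rank evidence is as strong as it can be.

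**Step 4: size of the bias.** The expected value of d is the true value divided by J, where J ≈ 1 − 3/(4·df − 1).
- Paired, SD of change, n = 9, df = 8: J = 1 − 3/31 = 0.903; 1/J = 1.107. The exact gamma-function form gives 10.8%.
- Between groups, pooled SD, df = 18 − 2 = 16: J = 1 − 3/63 = 0.952; 1/J = 1.050, or 5.0%. This depends only on the total, so it holds for any split of 18.
- Paired, other group sizes (exact form): 25.3% at n = 5 and 6.8% at n = 13.

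Of 18 people the smaller group has at most 9, so its paired inflation is at least about 11% whatever the split. Simulation with normal data agrees: a true 0.50 averages 0.553 (paired, n = 9) and 0.524 (9 against 9).

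**Step 5: bias against sampling error, at a true d of 0.50.**
- Paired, n = 9: SE ≈ √(1/9 + 0.25/18) = 0.35; bias 0.053, about one-seventh of the SE.
- Between groups: SE ≈ √(2/9 + 0.25/36) = 0.48; bias 0.024, about one-twentieth of the SE.

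**Step 6: exact against asymptotic p-values.**
- Assumed n = 5, all changes in one direction: z = (15 − 7.5)/√(5·6·11/24) = 2.02, p = 0.043. The exact p is 2/2⁵ = 0.0625. Only the approximation crosses 0.05.
- Assumed n = 9 without ties: a rank sum of 5 gives exact 20/512 = 0.039 and asymptotic 0.038; a rank sum of 6 gives exact 28/512 = 0.0547 and asymptotic 0.0506. The two methods agree about 0.05 here.

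**The case against.** The strongest reply is that the plain error, the misuse of the theorem, changes no analysis. Wilcoxon is sound for paired data at this size, and Kruskal–Wallis with two groups is equivalent to the asymptotic Mann–Whitney test. This stands. A reader might infer from the faulty reason that the tests themselves are wrong; nothing in the document supports that.

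Second, means, SDs and d are descriptive and need no normality. Choosing rank tests does not reject the measurement scale, and two different summaries may always disagree. This stands in part: the pairing is a mismatch, not a miscalculation. A measure that matches the test is still the better choice and costs nothing.

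Third, the bias is small, proportional to the true effect, zero when there is none, and alters no p-value. The 11% also presumes the SD of change as divisor, which the article does not say. All of this stands and limits the weight of the point.

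Fourth, the article does not mention intervals, exact p-values or the standardising SD, but a condensed article may leave these to a fuller document. A reader might infer that the plan excludes intervals or commits to asymptotic p-values. It says neither, so their absence is no finding; they belong only to the remedy. The group of 5 is likewise an illustration, not a feature of the plan.

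**Conclusion.** The point holds as a cheap improvement. The central-limit rationale is wrong and the Shapiro–Wilk step has no stated role, but correcting both changes no result. What affects the output is the choice of uncorrected Cohen's d beside rank tests. Its upward bias is about 5% between groups (18 analysed, pooled SD). For paired change it is about 11% with an assumed 9 per group and the SD of change as divisor, and more in a smaller group. This is well inside sampling error and does not produce false positives. Exact p-values could matter if a group proves very small, which the document neither states nor rules out.

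**What to change.** Change section 3.1.11 as follows.

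- Replace the central-limit sentence with a plain reason: small and possibly skewed samples.
- Drop Shapiro–Wilk, or label it descriptive with no bearing on the choice of test.
- Report the Hodges–Lehmann change within each group, and the Hodges–Lehmann between-group difference in change, each with an exact 95% confidence interval.
- If a standardised effect is kept, use Hedges' g in place of Cohen's d and name the standardising SD for the paired and the between-group comparison.
- Specify exact p-values for the rank tests. In a group of 5, the widest exact interval has coverage of only 1 − 0.0625 = 93.75%, so state the level attained if a group is that small.

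The cost is some wording and a few lines of analysis syntax, with no change to recruitment, assessments or data. The downside is that standardised effects shrink by about 5% between groups (1 − 0.952) and about 10% for paired change at 9 per group (1 − 0.903), and by more in a smaller group. In a very small group, a result that crosses 0.05 only by approximation would no longer do so.

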## 4. Discussion

This pilot study aims to evaluate the effects of a 12-week physical exercise program on anthropometric variables, body composition, cardiovascular response, and cardiorespiratory fitness in young people and adults with ASD. The results are expected to confirm the hypothesis that physical exercise provides significant physiological benefits based on adaptations in the cardiovascular and musculoskeletal systems, contributing to an overall increase in exercise capacity. These results should reinforce the use of exercise as an effective tool in the prevention and treatment of cardiometabolic diseases, the promotion of physical fitness, the improvement of performance in activities of daily living, and the reduction in restrictive and repetitive behaviors often observed in individuals with ASD.

The pilot study that will follow is essential to understand whether this exercise program is effective in reducing the barriers that hinder the practice of physical exercise by young people and adults with ASD, taking into account the low levels of physical fitness of this population [5,6,7], revealing a strong multidisciplinary approach, since it is prudent to evaluate the combined effects of exercise with independent variables. The exercise program will be supported by a quarterly plan, which includes the number of sessions, the didactic function of each session, the distribution of content per session, and the list of materials.

As with all studies, ours has some limitations, among which we highlight the following: (i) due to logistical constraints, it will not be possible to randomize the groups; (ii) due to limitations in recruiting participants, it will not be possible to implement a control group and (iii) it will not be possible to control the physical activities carried out outside the exercise program, which could positively or negatively influence the variables studied.

We intend to contribute with implications for practice with new interventions with physical exercise, prescription, and effective strategies, which we believe can contribute, at all levels, to the well-being of individuals with ASD. If the program proves to be effective, it could be implemented in institutions, schools, or clinics specializing in the prevention and treatment of symptoms in young people and adults with ASD, resulting in a tool to improve health-related QoL, but it will also promote greater inclusion and participation in regular physical activities, contributing to the general well-being of this population.

## 5. Conclusions

Just as important as the strategies to be implemented when carrying out training programs is the investment that the physical exercise technician (PET) will have to make in order to have a close relationship with individuals with ASD [56]. A relationship based on friendship and mutual respect will lead to the participant trusting the tasks proposed to them, accepting them, and facing them with greater motivation and enjoyment, which will facilitate the path taken and the achievement of objectives. The PET will have to get to know each participant well; they should have the opportunity to observe them in different contexts of life, getting to know their experiences and circumstances. At times of greater resistance, if this relationship is not cemented, it will be difficult to fulfill the training plan prescribed for the session. It is in the PET’s best interest, in addition to specific knowledge of adapted physical activity, to consider particular approaches to populations with neuro-atypical development.

## Figures and Tables

**Figure 1 jcm-13-05740-f001:**
[figure not shown]
Study design timeline.

**Table 1 jcm-13-05740-t001:** Physical Exercise Program [+ Life].

1st Month—Level I										
**Objectives—Exploring the different body segments, ranges of motion, and planes of movement; identifying weight distribution across supports; controlling breathing patterns in aerobic and strength exercises.**										
Walk—Line up and walk around the pavilion.				Duration	Interval	Speed	Intensity	Repetition	Series	Volume
				10 min	1 min	Walk	50–60% HR Max			10 min
Upper Limb Strength		Trunk Strength	Lower Limb Strength							
1st Circuit	UL lateral raise	Abdominal crunch	Stand up and sit down	20 min	1 min	Maximum Concentric Eccentric 3 s	Modified Borg Scale (0–10)	8	1	60 min
2nd Circuit	Flexion on an inclined plane (wall)	Pelvic lift	Hip abduction	20 min	1 min					
3rd Circuit	Flexion on an inclined plane (foam step)	Worm	Unilateral knee extension	20 min	1 min					
4 static stretches				30 s				1	1	1.5 min
2nd Month—Level II										
**Objectives—Emphasize unilateral strength work and symmetry between sides; strengthen the muscles of the upper and lower limbs; improve breathing control in higher-intensity exercises.**										
Walk/Run—In a line, run around the pavilion and then walk around the pavilion until you have completed the time set for the exercise.				Duration	Interval	Speed	Intensity	Repetition	Series	Volume
				10 min	1 min	Walk and Run	60–70% HR Max			10 min
Upper Limb Strength		Trunk Strength	Lower Limb Strength							
1st Circuit	Lateral elevation of UL with a moderate-resistance elastic band	Butterfly sit-ups	Stand up and sit down unipodally	20 min	1 min	Maximum Concentric Eccentric 3 s	Modified Borg Scale (0–10)	10	2	80 min
2nd Circuit	Bicep curls with a moderate-resistance elastic band	Pelvic lift with unipodal support	Hip abduction with shin guards (1 kg)	20 min	1 min					
3rd Circuit	Deadlift with bar	Plank with UL elevation	Unilateral knee extension with shin pads (1 kg)	20 min	1 min					
4th Circuit	UL flexion and extension with a disk (0.5 Kg)	Trunk extension	Step up and down (15 cm)	20 min	1 min					
4 static stretches				30s				1	1	1.5 min
3rd Month—Level III										
**Objectives—Progressively increase range of motion; increase cardiorespiratory capacity and muscular endurance; monitor and adjust breathing patterns.**										
Run—Line up and run around the pavilion.				Duration	Interval	Speed	Intensity	Repetition	Series	Volume
				10 min	1 min	Run	70–80% HR Max			10 min
Upper Limb Strength		Trunk Strength	Lower Limb Strength							
1st Circuit	UL rotation (front and back)	Basic jumping jacks	Lateral shift	15 min	1 min	Maximum Concentric Eccentric 3 s	Modified Borg Scale (0–10)	12	3	75 min
2nd Circuit	Lateral elevation of upper limbs with a high-resistance elastic band	Butterfly sit-ups	Static balance on a unipodal base	15 min	1 min					
3rd Circuit	Bicep curls with a high-resistance elastic band	Pelvic lift with unipodal support	Hip abduction with shin guards (2 kg)	15 min	1 min					
4th Circuit	Rope tsunami	Trunk extension	Unilateral knee extension with shin guards (2 kg)	15 min	1 min					
5th Circuit	UL flexion and extension with a disk (2.5 Kg)	Trunk extension with a ball (3 kg)	Step up and down (20 cm)	15 min	1 min					
4 static stretches				30 s				1	1	1.5 min
Static Stretching										
Upper Limb Strength		Trunk Strength	Lower Limb Strength	Duration		Series	Volume		Recovery	
While standing, interlace your toes and raise your upper limbs: above your head, in the midline of your shoulder and behind your back, in full extension, without ever lifting your feet off the ground.		Lying face down, place your hands under your body on the midline of your chest and lift your upper body up through them.	While standing, raise one of your legs to your chest; hold your ankle next to your buttock, placing your knee towards the ground, and flex your torso over your legs.	30 s		1	1.5 min		None	

HR Max—maximum heart rate; Kg—kilograms; min—minutes; s—seconds; %—percentage.

## Data Availability

The original contributions presented in the study are included in the article. Further questions can be addressed to the corresponding author.
